#### Sample size calculation.

Sample size estimation was performed in Stata (version 19.5) using the power pairedmeans command, based on a paired pre-post comparison of the primary outcome. Assuming a two-sided α of 0.05, 80% power, a standardised effect size of 0.40, and a within-subject correlation of 0.5, 52 evaluable patients were required. Allowing for potential loss to follow-up, a target sample size of 60 patients was set, providing approximately 86% power. Sensitivity analyses indicated that power ranged from 73% to 98% across plausible within-subject correlations (0.3–0.7).

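### The 86% power and its 73–98% range assume that all 60 patients are evaluable, yet 60 was set to allow for losses; with 52 evaluable, power is 81% (67–95%)

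*Protocol article*

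**What the plan says.** All the figures stand in the protocol article under *Sample size calculation*, which describes a paired pre-post comparison of means.

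- Requirement: "Assuming a two-sided α of 0.05, 80% power, a standardised effect size of 0.40, and a within-subject correlation of 0.5, 52 evaluable patients were required".
- Enrolment target: "Allowing for potential loss to follow-up, a target sample size of 60 patients was set, providing approximately 86% power".
- Sensitivity: "Sensitivity analyses indicated that power ranged from 73% to 98% across plausible within-subject correlations (0.3–0.7").

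The section gives no loss rate. It does not say how many evaluable patients lie behind the 86% or the 73–98% range. *Data management* says that everyone is expected to complete the visits. *Statistical analysis* names a paired t-test or Wilcoxon signed-rank test for the change in cerebral hemodynamics from baseline to 6 months. It also plans linear mixed models for repeated continuous outcomes.

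**The concern.** The step from 52 to 60 is explained as a reserve for patients who will not be evaluable. A patient held in reserve against loss cannot also add to the power of the analysis. If the reserve is needed, the analysis has about 52 pairs and the power of 52 pairs. If it is not needed, the power is that of 60 pairs. The text gives the reason for the first case and the power of the second, without stating the condition.

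The sensitivity range is affected most. Its purpose is to show how far power falls if the correlation is lower than planned. If it is computed on 60 complete pairs, it understates that fall for the number of patients the plan itself provides for.

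**Working it through.** **Inputs, all from *Sample size calculation*.** Two-sided α = 0.05; standardised effect d = 0.40; correlation ρ = 0.5, with a range of 0.3 to 0.7; 52 evaluable patients required; 60 enrolled. The reserve implied by these numbers is (60 − 52)/60 = 8/60 = 13.3%.

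**Formula.** With d in units of the SD of a single measurement, the SD of the paired difference is √(2(1 − ρ)) in the same units. The noncentrality parameter is

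δ = 0.40 / √(2(1 − ρ)) × √n.

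Power is the probability that a noncentral t variable with n − 1 degrees of freedom and noncentrality δ falls outside ± the 97.5% point of the central t.

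**Step 1: the required number.** At ρ = 0.5, √(2 × 0.5) = 1, so δ = 0.40√n.

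- n = 51: power 79.99%.
- n = 52: δ = 2.884, power 80.8%.

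The smallest n that reaches 80% is 52, as stated. This confirms the reading of the effect size.

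**Step 2: the stated power figures.** With n = 60:

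| ρ | δ | Power, 60 pairs | Stated |
|---|---|---|---|
| 0.3 | 2.619 | 73.1% | 73% |
| 0.5 | 3.098 | 86.2% | about 86% |
| 0.7 | 4.000 | 97.6% | 98% |

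All three match, so the stated figures are those for 60 complete pairs.

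**Step 3: the same calculation with 52 evaluable.**

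| ρ | δ | Power, 52 pairs | Shortfall against 60 pairs |
|---|---|---|---|
| 0.3 | 2.438 | 66.7% | 6.4 points |
| 0.5 | 2.884 | 80.8% | 5.4 points |
| 0.7 | 3.724 | 95.5% (0.9548, so 95% as a whole number) | 2.1 points |

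**Step 4: partial loss.** At ρ = 0.5, power is 82.3% with 54 pairs, 83.7% with 56 and 85.0% with 58. At ρ = 0.3 with 58 pairs it is 71.6%.

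**Step 5: what a mixed model could recover.** Suppose 52 patients have all three ASL scans and eight have only the baseline and early postoperative scans, with equal correlation between all time points (an assumption). The information on the change from baseline to 6 months then equals that of about 54 to 55 complete pairs. Power is about 82.5% at ρ = 0.5 and 69% at ρ = 0.3.

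**The case against.** The strongest reply is that no stated number is miscalculated. Sixty patients do give 86% power if all complete, and *Data management* expects them to. The text also says that 52 evaluable patients give 80%, so a careful reader can see both ends of the base case. No loss rate is stated, so 52 is an inferred floor and not a forecast. The mixed model can use incomplete records, so a patient lost before 6 months is not wholly wasted. Finally, the article concedes under *Limitations* that 60 was chosen mainly on feasibility and may limit power.

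Much of this stands. The fault is an unstated condition rather than a wrong formula, and it leaves the choice of 60 intact. Three points remain:

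- An expectation of full completion does not fit with making an allowance for loss. Having made the allowance, the plan should give the power that goes with it.
- The 80% at 52 covers only ρ = 0.5. Nothing in the text tells the reader that the low end of the range is 67% with 52 evaluable patients.
- The mixed model narrows the gap but does not restore 86%, as step 5 shows. The power calculation is for paired means, and a paired test is what *Statistical analysis* names for the hemodynamic outcome.

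**Conclusion.** The point holds. The 86% and the 73–98% range are no-loss figures, placed in and directly after a sentence that justifies 60 by expected loss. With the 52 evaluable patients the plan requires, they become 81% and 67–95%. The overstatement is about 5 points at ρ = 0.5 and 6 points at ρ = 0.3.

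The effect is modest. The base case still meets its 80% target at 52, so the sample size does not fail. At ρ = 0.3 the target is missed either way: 73% with no loss, 67% with the full allowance used.

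This rests on the protocol's own inputs, on the paired t-test as the analysis, and on reading 52 as the number left once the allowance is used. With smaller losses the true figure lies between the two sets.

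**What to change.** Replace the two power sentences with one that gives both cases, for example: *With 52 evaluable of 60 enrolled (a loss of 8/60, 13%), power is 81% at a within-subject correlation of 0.5 and 67% to 95% for correlations of 0.3 to 0.7; if no patient is lost, the figures are 86% and 73% to 98%.* If the sponsor planned on a different loss rate, state it and give the power at the resulting evaluable number.

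The sentence should also say that the figures refer to the change in cerebral hemodynamics. The calculation is for paired means of what that section calls the primary outcome, whereas *Definitions of outcomes* makes ischemic stroke incidence primary, and paired-means power does not apply to that.

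The cost is one sentence and a slightly less favourable headline figure. Enrolment, design and analysis do not change.

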### Statistical analysis

Continuous variables will be reported as mean with standard deviation or median with interquartile range, depending on distribution. Categorical variables will be presented as frequencies and percentages. The primary outcome, change in cerebral hemodynamic status from baseline to 6 months, will be analyzed using a paired t-test or Wilcoxon signed-rank test, depending on data distribution. Mean change in CBF and/or perfusion asymmetry will be reported with 95% confidence intervals.

Early postoperative and 6-month changes in neurological and cognitive scores will be analyzed using paired tests. Categorical outcomes, including graft patency, recurrent TIA or stroke, complications, and mortality, will be reported as proportions with 95% confidence intervals.

Where appropriate, exploratory regression analyses will be performed to identify factors associated with hemodynamic improvement and clinical outcomes. Potential predictors may include age, sex, baseline perfusion deficit, vascular risk factors, duration of symptoms, and preoperative neurological status. Given the limited sample size, multivariable models will be restricted to a small number of clinically relevant covariates.

Because repeated measurements will be obtained from the same participants, analyses will account for within-subject correlation. Continuous repeated outcomes will be analysed using linear mixed-effects models, with time point entered as a fixed effect and participant ID as a random intercept. This approach allows estimation of postoperative change while accounting for correlation between repeated measures within individuals and accommodating incomplete follow-up data under a missing-at-random assumption.

A p-value <0.05 will be considered statistically significant. All analysis will be performed using Stata 19.5.

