**Methods:**

This single-centre, prospective, open-label interventional longitudinal study includes 60 patients with chronic internal carotid artery occlusion undergoing superficial temporal artery-to-middle cerebral artery (STA–MCA) bypass at National Centre for Neurosurgery in Kazakhstan. The primary endpoint of the study is the incidence of ischemic stroke during the 6-month follow-up period after surgery. Pre- and postoperative evaluations include detailed angiographic assessment of collateral circulation and donor vessel diameter, as well as cerebral perfusion imaging using arterial spin labelling MRI. Neurological and cognitive function are assessed using standardized clinical and neuropsychological tests. Early and six-month follow-up evaluations focus on bypass patency, perfusion changes, and clinical outcomes.

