To address these knowledge gaps, this prospective single-arm interventional cohort study aims to evaluate hemodynamic, neurological, and cognitive outcomes following STA-MCA bypass in patients with chronic ICA occlusion and documented cerebral hypoperfusion. The primary endpoint is the incidence of recurrent ischemic cerebrovascular events, defined as ischemic stroke or transient ischemic attack occurring within 6 months after surgery. The secondary endpoints include postoperative neurological and cognitive improvement, assessed using standardized neurological and neuropsychological measures, and their relationship with changes in cerebral perfusion assessed using arterial spin labeling magnetic resonance imaging and angiographic parameters of revascularization. Specifically, the study aims to investigate whether postoperative hemodynamic improvement correlates with neurological recovery and cognitive trajectories following revascularization. By integrating radiological, perfusional, and functional assessments, this study seeks to improve prognostic evaluation and refine patient selection for surgical revascularization in chronic carotid artery occlusive disease.

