### Study objectives

#### Primary objective.

To evaluate the incidence of ischemic stroke during the 6-month follow-up period after surgery.

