#### Definitions of outcomes.

The primary outcome is defined as the incidence of ischemic stroke during the 6-month follow-up period after surgery. This outcome will be assessed based on clinical evaluation and confirmed by neuroimaging (MRI or CT) in cases of suspected new neurological deficits, in accordance with standard diagnostic criteria for ischemic stroke.

Secondary outcomes included early postoperative haemodynamic change (≤7 days) assessed using the same imaging modality; graft patency was defined as uninterrupted flow through the bypass on intraoperative ICG and postoperative CTA; changes in cerebral haemodynamic status from baseline to 6 months after surgery will be assessed using ASL MRI and defined as a quantitative increase in regional CBF in the affected hemisphere and/or a reduction in interhemispheric perfusion asymmetry compared with baseline; change in neurological status from baseline to 6 months assessed using the NIHSS and the mRS; changes in cognitive function from baseline to 6 months based on standardised neuropsychological testing; all-cause mortality at 6 months; perioperative complications within 30 days (including intracranial haemorrhage, hyperperfusion syndrome, seizures, wound complications, and graft occlusion); and angiographic extent of revascularisation on follow-up imaging.

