### Ethics

Prior to registration, all participants will provide written informed permission in compliance of the Declaration of Helsinki’s ethical guidelines.

Patient confidentiality will be ensured through strict coding and anonymization of personal identifiers and medical record identification numbers (MRINs).

Institutional Review Board Statement: The study will adhere strictly to scientific ethics principles, including prevention of data fabrication, falsification, plagiarism, and false authorship. The study protocol and other necessary documents were reviewed and approved by the ethics committee (Protocol No. 4 of September 25, 2024, S2 Appendix). This study was retrospectively registered on ClinicalTrials.gov (NCT07396025; February 5, 2026) due to an administrative delay that prevented registration before participant enrolment; however, the study protocol, eligibility criteria, intervention, and outcome measures were predefined prior to recruitment and remained unchanged after registration. This study will be conducted according to the principles of the Declaration of Helsinki and subsequent amendments.

Informed Consent Statement: Written informed consent has been obtained from the patient(s) to publish this paper.

The authors confirm that all ongoing and related trials for this drug/intervention are registered.

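### Three different outcomes are called primary, and the sample size and the only test labelled primary fit hemodynamic change, not the declared stroke endpoint

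*Protocol article*

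**What the plan says.** The protocol article gives the primary label to three outcomes.

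- **Ischemic stroke over 6 months.** The abstract (Methods) says "The primary endpoint of the study is the incidence of ischemic stroke during the 6-month follow-up period after surgery". The Primary objective and Primary endpoint sections say the same, and Definitions of outcomes confirms it: "The primary outcome is defined as the incidence of ischemic stroke during the 6-month follow-up period after surgery".
- **Ischemic stroke or TIA over 6 months.** The last paragraph of the Introduction names as primary endpoint the "incidence of recurrent ischemic cerebrovascular events, defined as ischemic stroke or transient ischemic attack occurring within 6 months after surgery".
- **Hemodynamic change.** Statistical analysis opens its inferential plan with "The primary outcome, change in cerebral hemodynamic status from baseline to 6 months" and assigns it a paired t-test or a Wilcoxon signed-rank test.

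Two of these are also classed as secondary. Definitions of outcomes places among the secondary outcomes that "changes in cerebral haemodynamic status from baseline to 6 months after surgery will be assessed using ASL MRI". The Secondary endpoints section includes recurrent cerebrovascular events.

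Sample size calculation uses paired means of an unnamed primary outcome: two-sided alpha 0.05, 80% power, standardised effect 0.40 and within-subject correlation 0.5. It reports 52 evaluable patients, 60 enrolled, about 86% power at 60, and 73% to 98% over correlations of 0.3 to 0.7.

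The Ethics section reports that the study was registered retrospectively, and states that "outcome measures were predefined prior to recruitment and remained unchanged after registration".

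**The concern.** The primary endpoint is the one result a reader should be able to identify before the data exist. Here the sections that define outcomes point to a binary clinical event, while the section that analyses them points to a continuous imaging measure. The Introduction adds a third, composite event. Depending on which section is followed, the headline could be a stroke proportion, a stroke-or-TIA proportion, or a mean perfusion change with a p-value.

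Two consequences follow. First, the stated power is attached to something other than the declared primary, so a reader would credit the stroke endpoint with a statistical basis that it lacks. Second, with registration after enrolment had begun, the assurance that outcomes were fixed beforehand has to be borne out by the document, and a text with three primaries does not bear it out.

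**Working it through.** **1. The sections side by side**

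| Section | Outcome called primary | Type |
|---|---|---|
| Abstract, Methods | Ischemic stroke | Binary event |
| Introduction, last paragraph | Ischemic stroke or TIA | Binary composite |
| Primary objective; Primary endpoint; Definitions of outcomes | Ischemic stroke | Binary event |
| Sample size calculation | Not named; compared before and after by paired means | Continuous, paired |
| Statistical analysis | Change in cerebral hemodynamic status | Continuous, paired |
| Limitations | Primary objective described as studying hemodynamic, neurological and cognitive changes | Mixed |

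All of this is current text, and no sentence reconciles the versions. Four sections favour stroke alone, but the calculation and the test favour hemodynamic change, so counting sections does not settle the matter.

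**2. Reproducing the plan's sample size**

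Inputs are from Sample size calculation: effect 0.40, correlation ρ, two-sided alpha 0.05. The standardised paired difference is d_z = 0.40 / √(2(1 − ρ)). Power comes from the noncentral t distribution with n − 1 degrees of freedom and noncentrality d_z·√n.

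- ρ = 0.5: d_z = 0.40/√1 = 0.40. Power is 79.99% at n = 51 and 80.8% at n = 52, so 52 are required. At n = 60 it is 86.2%.
- ρ = 0.3: d_z = 0.40/√1.4 = 0.338. Power at 60 is 73.1%.
- ρ = 0.7: d_z = 0.40/√0.6 = 0.516. Power at 60 is 97.6%.

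Every stated figure (52, about 86%, 73% to 98%) is reproduced. The arithmetic is right.

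**3. Which outcome it belongs to**

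The calculation needs a value per patient before and after surgery, a standardised mean difference and a within-subject correlation. Six-month postoperative stroke incidence has none of these, and nor does stroke or TIA. Among the three candidates only hemodynamic change fits. For stroke the protocol gives no expected rate, reference rate or target precision, so no required sample size or power can be derived.

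**4. What 60 patients provide for an event endpoint**

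The protocol gives no event rate, so the counts below are assumptions. Intervals are exact (Clopper-Pearson) 95%; for zero events the upper limit is 1 − 0.025^(1/n).

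| Events | n = 60 | n = 52 |
|---|---|---|
| 0 | 0% (0 to 6.0%) | 0% (0 to 6.8%) |
| 3 | 5.0% (1.0 to 13.9%) | 5.8% (1.2 to 15.9%) |
| 6 | 10.0% (3.8 to 20.5%) | 11.5% (4.4 to 23.4%) |
| 9 | 15.0% (7.1 to 26.6%) | 17.3% (8.2 to 30.3%) |

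The choice between stroke and stroke-or-TIA also moves the headline. If, for illustration, 3 of 60 patients had a stroke and 3 others a TIA only, the primary result would be 5.0% under Definitions of outcomes and 10.0% under the Introduction.

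**The case against.** The best defence is that the harm is limited. The study is single-arm, states no success criterion, and its Discussion disclaims any comparison with conservative treatment. Statistical analysis commits to reporting both the hemodynamic change and the events, so neither would be suppressed. That stands: what is open is which result is presented as primary, not whether a result appears.

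A reader might infer several stronger claims that the document does not support.

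- *That stroke has no analysis.* Statistical analysis reports categorical outcomes, including TIA or stroke, as proportions with 95% confidence intervals, which is a usable analysis of incidence. What is lacking is the primary label and an unambiguous line for stroke alone.
- *That one of the three results decides the trial, or that they could point in opposite directions.* An uncontrolled incidence with no reference rate is neither positive nor negative. The trial cited in the Introduction, with better hemodynamics but no reduction in stroke, was reporting on stroke reduction, which this study cannot measure.
- *That the outcome was switched.* The registered outcome is not visible in the document, and nothing in it shows a change.
- *That stroke must be the intended primary because most sections say so.* The sample size and the primary test point the other way, so only the sponsor can say which outcome was predefined.

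**Conclusion.** The contradiction is explicit, and a separate analysis plan could not remove it, because the protocol's own sections disagree. Three outcomes carry the primary label, and the 52/60 and 86% figures, although correctly computed, fit the hemodynamic outcome and not the declared stroke endpoint. The result to be headlined is therefore not fixed, and the Ethics statement on predefined outcomes is not borne out by the text.

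The size of the problem depends on which outcome is kept. If it is stroke, the primary has no stated statistical basis beyond the precision of about 60 patients. If it is hemodynamic change, the power stands at 86% under an effect of 0.40 and correlation 0.5 (73% to 98% over the plan's own range), but four sections and the Introduction misstate the primary. The event counts used above are illustrative. This should be corrected before results are analysed.

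**What to change.** The sponsor should state which single outcome was predefined as primary, name it identically in the abstract, Introduction, Primary objective, Primary endpoint, Definitions of outcomes, Sample size calculation, Statistical analysis and Limitations, and disclose the correction in view of the retrospective registration.

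**If it is ischemic stroke:**
- In Statistical analysis, relabel hemodynamic change as secondary and add a stroke-alone primary analysis: 6-month incidence with an exact 95% confidence interval and a stated rule for deaths and patients lost to follow-up. A time-to-event or competing-risk version would also be acceptable but is not required.
- In the Introduction, make stroke or TIA a secondary composite.
- In Sample size calculation, say that 52/60 and 86% apply to the secondary hemodynamic outcome, and give the precision of 60 patients for stroke, for example the intervals tabulated above.

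**If it is hemodynamic change:**
- Name one measure, either CBF or perfusion asymmetry, since the present wording allows either or both.
- Correct the abstract, Introduction, Primary objective, Primary endpoint and Definitions of outcomes. The sample-size figures then stand.

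The cost is wording only, with no new data or patients. The drawback of keeping stroke is that the protocol can no longer quote 86% power for its primary endpoint.

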### Eligibility criteria

#### Inclusion.

Chronic ICA occlusion confirmed by computed tomography angiography (CTA), magnetic resonance angiography (MRA), and digital subtraction angiography (DSA).Evidence of cerebral hypoperfusion on magnetic resonance imaging (MRI) arterial spin labelling (ASL) within the territory of the occluded ICA, defined as a ≥ 30% reduction compared with the contralateral hemisphere.Modified Rankin Scale (mRS) score of 0–3 at baseline.Preserved language comprehension, with no more than mild motor aphasia and no significant cognitive impairment.Adults aged 18–80 years.Provision of written informed consent by the patient or a legally authorised representative.Willingness and ability to comply with follow-up assessments.

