**Hemodynamic parameters**				
Collateral circulation patterns	+			
Location and length of the internal carotid artery occlusion	+			
Circle of Willis configuration	+			
ASL perfusion metrics	+	+	+	
Cerebral blood flow (CBF) asymmetrical indices	+	+	+	
Infarct burden	+	+	+	
White matter hyperintensities	+			
Bypass patency and the diameter of STA		+	+	+

Abbreviations: Preop – preoperatively, PostOp0 – Immediately postoperatively, PostOp6–6 months postoperatively, UV – Unscheduled Visit, TIA – transient ischemic attack, BMI – Body mass index.

Included patients will undergo CTA of the head and neck vessels with a slice thickness of 0.5-0.625 mm to confirm ICA occlusion and to measure the diameter of the donor STA branch at 2 mm distal to its bifurcation.

MRI perfusion studies will be conducted before surgery on 1.5 or 3 Tesla MRI to evaluate cerebral blood flow (CBF) and determine the extent of cerebrovascular insufficiency. The main perfusion method will be ASL, which will provide quantitative CBF values, assess the degree of perfusion deficit, and reveal signs of compensatory collateral circulation based on the presence of arterial transit artifacts (ATA). Imaging parameters are described in in S1 Table.

DSA will be performed using a biplane digital subtraction angiography system (Artis Zee, Siemens) with a 6F guiding catheter at a frame rate of 7.5 frames per second. The angiographic assessment will evaluate the presence of communicating arteries, the completeness of the Circle of Willis, and the extent of collateral circulation. Hemodynamic compensation will be quantified by analyzing filling times and phase delays across the arterial, parenchymal, and venous phases, expressed in frames. Image analysis will be conducted using Siemens Artis Q angiography software to ensure accurate and reproducible measurements.

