#### Postoperative study procedures.

Within 1-3 days after surgery, CTA of the head and neck will be performed to confirm bypass patency, measure the caliber of the donor STA branch, and visualize its course. At 3–5 days postoperatively, ASL-based MR perfusion imaging will be conducted to evaluate cerebral perfusion changes compared with preoperative studies. 3D segmentation and quantitative perfusion mapping will be applied to provide an objective assessment of regional perfusion improvements following surgery. Before hospital discharge, all patients will undergo a repeat evaluation of neurological status and cognitive function using the same standardised tests as preoperatively.

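### The single scheduled pre-operative ASL scan appears to serve as entry test, baseline for change and predictor of change, so regression to the mean biases the asymmetry result towards improvement

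*Protocol article*

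**What the plan says.** - **Entry.** The inclusion criteria require "Evidence of cerebral hypoperfusion on magnetic resonance imaging (MRI) arterial spin labelling (ASL) within the territory of the occluded ICA", with the threshold set at no less than a "30% reduction compared with the contralateral hemisphere".
- **Scans.** Table 1 marks MRI ASL in one pre-operative column, then immediately after surgery and at 6 months. The text says that "MRI perfusion studies will be conducted before surgery on 1.5 or 3 Tesla MRI", and no repeat or separate qualifying scan is described. The early post-operative scan is likewise compared with the pre-operative one: "ASL-based MR perfusion imaging will be conducted to evaluate cerebral perfusion changes compared with preoperative studies".
- **Outcome.** Definitions of outcomes counts as haemodynamic change a rise in regional CBF in the affected hemisphere and/or "a reduction in interhemispheric perfusion asymmetry compared with baseline". The entry metric is therefore also an outcome metric.
- **Test.** Statistical analysis states: "The primary outcome, change in cerebral hemodynamic status from baseline to 6 months, will be analyzed using a paired t-test or Wilcoxon signed-rank test".
- **Predictors.** The same section says that "exploratory regression analyses will be performed to identify factors associated with hemodynamic improvement and clinical outcomes", and continues: "Potential predictors may include age, sex, baseline perfusion deficit, vascular risk factors, duration of symptoms, and preoperative neurological status".
- **Limitations.** These name selection bias, the missing control group, residual confounding and the exploratory status of multivariable models. They do not name regression to the mean.

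**The concern.** Two separate problems follow from using one noisy measurement three times.

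First, a patient near the 30% cut is more likely to enter when measurement error exaggerates the asymmetry. That error is not repeated at 6 months, so mean asymmetry falls even if surgery changes nothing. A paired test against zero counts the fall as improvement, and there is no control arm in which the same fall would show.

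Second, if improvement is analysed as a change score, the baseline value sits on both sides of the regression. A larger baseline deficit then goes with a larger gain by arithmetic.

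The planned mixed model, with time as a fixed effect and a random intercept, removes neither problem. At stake are the hemodynamic result and the stated aims of identifying predictors of successful revascularisation and refining patient selection. The study could report that the worst-perfused patients gain most when nothing of the kind is true.

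**Working it through.** **1. The plan's own figure.** Inputs from Sample size calculation: two-sided alpha 0.05, 80% power, standardised effect 0.40, within-subject correlation 0.5. The effect in units of the SD of the difference is 0.40/√(2(1 − 0.5)) = 0.40. With the noncentral t distribution, power is 80.8% at 52 patients and 86.2% at 60. At correlations 0.3 and 0.7 and 60 patients it is 73.1% and 97.6%. The stated 52, 86% and 73% to 98% all reproduce. The calculation is sound, but it treats zero as the change expected without an effect.

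**2. Model with zero true change.** Let X be the observed asymmetry at the pre-operative scan and Y that at 6 months, both in SDs of the screened population, bivariate normal with test-retest correlation r. A share p of screened patients passes the cut c. Neither r nor p is given in the protocol, so both are assumptions.

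- Mean of X in those enrolled: λ = φ(c)/p. Variance: v = 1 + cλ − λ².
- Gain G = X − Y. Its mean is (1 − r)λ and its SD is √((1 − r)²v + 1 − r²).
- Correlation of X with G in those enrolled: (1 − r)√v / SD(G).

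For p = 0.5: c = 0, λ = 0.798, v = 0.363. For p = 0.8: c = −0.842, λ = 0.350, v = 0.583.

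Example, p = 0.5 and r = 0.5: mean gain 0.5 × 0.798 = 0.399; SD(G) = √(0.25 × 0.363 + 0.75) = 0.917; ratio 0.435; correlation of X with G = 0.5 × 0.603/0.917 = 0.33.

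**3. Results, 60 patients.** Rates are simulated and good to about one percentage point.

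| p | r | Spurious gain (population SD) | Paired test declares improvement (nominal 2.5%) | Correlation of baseline with gain | Baseline falsely associated with gain |
|---|---|---|---|---|---|
| 0.5 | 0.5 | 0.40 | 92% | 0.33 | 73% |
| 0.5 | 0.7 | 0.24 | 70% | 0.25 | 47% |
| 0.5 | 0.9 | 0.08 | 28% | 0.14 | 19% |
| 0.8 | 0.5 | 0.17 | 29% | 0.40 | 90% |
| 0.8 | 0.7 | 0.10 | 18% | 0.31 | 67% |
| 0.8 | 0.9 | 0.03 | 9% | 0.17 | 26% |

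The two problems move in opposite directions with p. A stricter cut enlarges the spurious mean gain but narrows the baseline range, which weakens the false association.

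**4. What the planning correlation of 0.5 implies.** That figure belongs to the trial's paired comparison, hence to enrolled patients. The correlation in those enrolled is r√v/√(r²v + 1 − r²). With p = 0.5 and r = 0.69 this is 0.416/0.835 = 0.50. An enrolled correlation of 0.5 therefore corresponds to a screened r of about 0.69, with a spurious gain of (1 − 0.69) × 0.798 = 0.25 SD.

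**The case against.** - **The scans may not be the same.** The protocol never says in words that the qualifying scan is the baseline. This stands as a caveat: it is inferred from the single pre-operative column and the absence of any other scan.
- **The dependent variable is not fixed.** The protocol speaks of hemodynamic improvement and does not define it as follow-up minus baseline in the regression; nor does it say that neurological change is regressed on preoperative status. The list is permissive and the models exploratory. This stands, and it makes the predictor problem conditional. It does not touch the paired test.
- **Primary outcome and disclaimers.** The objectives and endpoints make ischemic stroke primary, although Statistical analysis gives that label to hemodynamic change; that conflict is a separate matter. The article also disclaims comparative efficacy and causal inference. This limits the consequence, but regression to the mean biases the descriptive change itself, and adjustment for confounders does not remove it.

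Four stronger readings are tempting and not supported:

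- A reader might infer that the false predictor is almost certain, since an untruncated baseline with correlation 0.5 gives 98.6% rejection. That ignores the entry cut, which is the very source of the mean bias; with half qualifying the rate is about 73%.
- A reader might note that the spurious 0.40 SD equals the planned effect. The match arises only if the enrolled-patient correlation of 0.5 is moved to the screened population; step 4 gives about 0.25 SD instead.
- A reader might conclude that any observed improvement is artefact. The documents fix only the direction of the bias. With a reliable scan and most patients well past the cut it is small (0.02 SD at r = 0.95 and p = 0.8).
- A reader might want baseline deficit dropped from the models. In a linear change-score model that contains the same baseline measure, the other predictors' coefficients equal those from modelling the 6-month value on baseline. Dropping it would make those estimates worse.

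**Conclusion.** The concern holds for the change in perfusion asymmetry and, if improvement is a change score, for baseline deficit as its predictor. Absolute CBF is affected less, because it is not the entry metric.

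The bias towards improvement is certain in direction. Its size depends on two quantities that the protocol does not give: the screened test-retest correlation and the share of screened patients who pass the cut. Over the values shown, the spurious gain runs from 0.03 to 0.40 population SD, and the chance of a false declaration of improvement from about 9% to 92%. The false baseline association runs from about 19% to 90%. All of this assumes normality, zero true change, 60 analysed patients and one scan serving as both entry test and baseline.

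**What to change.** 1. When studying other predictors, model the 6-month ASL, NIHSS and cognitive values with the corresponding baseline value as a covariate. Keep baseline in the model, but do not interpret the baseline-deficit coefficient as a predictor of perfusion benefit.
2. As a sensitivity analysis, report the 6-month change in asymmetry beside the regression to the mean expected for r from 0.5 to 0.9. Use the screening ASL values, including those below 30%, where they are available. Enrolment began in July 2025, so earlier values may be lost, but it runs to December 2027 and later ones can be kept. Because r is unknown, this should inform interpretation and not serve as a decision rule.
3. State in the limitations that a change in asymmetry different from zero is not by itself evidence of improvement.

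The cost is a little more analysis and a less favourable reported gain; no extra scan is needed. A second pre-operative scan, not used for entry, would remove the mean bias (the test then rejects in 4.6% to 5.2% of simulated null trials). It would not cure the predictor problem if that scan were again both baseline and predictor, and it is not requested here.
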